##### Pain levels

Pain levels will be assessed with the numerical rating scale (NRS) [28]. The NRS is an 11-point scale ranging from 0 to 10, where 0 defines absence of pain and 10 describes unbearable pain [28]. The weekly electronic questionnaire developed for the trial will gather average weekly pain levels based on the NRS [28].

##### Disability

Functional disability will be assessed with the Roland–Morris Disability Questionnaire (RDQ) [29]. It consists of 24 questions focusing on normal activities of daily life. Each affirmative answer corresponds to 1 point and the final score is determined by the total number of points. Total score ranges from 0 to 24 and higher scores indicate higher disability. Scores above 14 indicate severe impairment [30]. The weekly electronic questionnaire will also gather weekly disability impairment based on the RDQ.

### Secondary outcomes

Secondary outcomes will include:

*Physical activity:* Self-reported physical activity will be measured using the International Physical Activity Questionnaire (IPAQ) [31]. Objectively measured physical activity will be assessed over a 7-day period using a matchbox-sized accelerometer (*Actigraph* GT3X+). Participants will be instructed to wear the accelerometer on the right hip, attached via an adjustable elastic belt, for seven consecutive days during waking hours (except during water activities or bathing). Activity counts per second will be collected at a sampling frequency of 30 Hz and reintegrated to 60-second epochs for data analysis. The mean counts/minute/day ActiGraph measure will be computed as the total counts accumulated in a valid day divided by the wear time of that day. To be considered as a valid day for analysis, ActiGraph wear time must include 10 h or more. Periods of 60-minutes or more of consecutive zeros (indicating non-use) will be considered as “off-time”. Participants will receive a diary to record all their activities on their waking hours during the 7 days that they will be wearing the *Actigraph.* Accelerometer data will be manually checked against participant diary to verify wear time and erroneous data will be excluded prior to analysis.

*Goal attainment* will be assessed using the Goal Attainment Scale (GAS) [27]. Two long-term goals will be defined by the participant at trial entry GAS is a method used to evaluate interventions according to the attainment of a number of participant-specific goals. In effect, each participant has his/her own outcome measure but this is scored in a standardised way to allow proper statistical analysis. Traditional standardised measures include a standard set of tasks (items) each rated on a standard level. In GAS, tasks are individually identified to suit the participant, and the levels are individually set around their current and expected levels of performance [32]. According to a recent systematic review, GAS delivers reliable and valid scores when employed as an outcome measure in working age and older people within a physical and neurological rehabilitation environment [33].

### Sample size calculation

The sample size for this trial was determined in order to detect a 2-point difference between groups on the pain intensity outcome measured by the Pain Numerical Rating Scale, assuming a standard deviation of 1.9 points [34]. According to a study conducted by J. T. Farrar et al. [35], in a randomized controlled trial a raw change of 1.74 and a percent change of 27.9 % on a 0–10 pain intensity scale is a clinically important improvement [36].

The following specifications were used: statistical power of 80 %, alpha of 5 %. Anticipating maximum loss to follow-up of 35 % [37] the calculated target sample size is 68 patients (34 participants per group). As this is a pilot study, it will investigate the feasibility of conducting a randomized controlled trial (RCT) testing an innovative physical activity management strategy to prevent decline in clinical outcomes following conservative treatment for people with chronic LBP. Findings from this trial will inform on the feasibility, effect size and design of a large multi-centred RCT.

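### The target of 68 cannot be reproduced from the stated inputs, which give about 50; under those inputs the discrepancy is conservative

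*Protocol article*

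**What the plan says.** The Sample size calculation section of the protocol article gives a full set of inputs and one result:

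- Purpose: "to detect a 2-point difference between groups on the pain intensity outcome", measured on the Numerical Rating Scale.
- Variability: "assuming a standard deviation of 1.9 points".
- Error rates: "statistical power of 80 %, alpha of 5" per cent. Neither the sidedness of the test nor any split of alpha is mentioned.
- Attrition: "Anticipating maximum loss to follow-up of 35" per cent.
- Result: "the calculated target sample size is 68 patients (34 participants per group").

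The same section cites "a raw change of 1.74 and a percent change of 27.9 % on a 0–10 pain intensity scale" as clinically important, but the design difference is 2 points. The Abstract and the Participants section repeat 68 patients, 34 per group. The Statistical analysis section plans a linear mixed model, with the group-by-time interaction as the treatment effect.

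**The concern.** The article presents 68 as the output of a calculation and prints the inputs beside it, so a reader can repeat the sum. It does not come out. The gap is too large for rounding or for the choice between a normal and a t calculation: 68/50 = 1.36, so the target is 36%, or 18 patients, above what the inputs require.

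Either one of the printed figures (difference, SD, power, alpha, loss or target) is not the one used, or a step was left out. The text does not show which. That matters in two modest ways. The justification for the number recruited cannot be verified. And since the pilot is meant to inform a larger multi-centre trial, a wrong SD or power statement could be carried into its planning.

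**Working it through.** **Inputs, all from the Sample size calculation section:** difference δ = 2; SD σ = 1.9; power 80%; alpha 5%; loss 35%; equal groups. Assumption: two-sided test.

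**1. Attempt to reproduce the target.**

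Normal approximation, per group:
n = 2 (z₀.₉₇₅ + z₀.₈₀)² (σ/δ)² = 2 × (1.960 + 0.842)² × (1.9/2)² = 2 × 7.85 × 0.9025 = 14.17, so 15.

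Exact noncentral t calculation: n = 15.19, so 16.

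Inflation for loss, n/(1 − 0.35):
- normal: 15/0.65 = 23.1, so 24 per group, **48 in total**;
- t: 16/0.65 = 24.6, so 25 per group, **50 in total**.

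The stated figure is 34 per group, 68 in total. It is not reproduced. For 34 per group to leave just 16, loss would have to be 1 − 16/34 = 53%, not 35%.

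**2. Other readings that keep the stated alpha, power, SD and loss.**

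| Variant | Evaluable per group | Randomised in total |
|---|---|---|
| One-sided 5%, δ = 2 | 12 | 38 |
| Two-sided, inflation by × 1.35 instead of ÷ 0.65 | 15 to 16 | 42 to 44 |
| Two-sided, rank-test allowance (efficiency 0.955 or 0.864) | 17 or 19 | 54 or 60 |
| Two-sided, δ = 1.74 | 19 (normal) or 20 (t) | 60 or 62 |

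None gives 68. Dropping the two-sided assumption widens the gap.

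**3. What would have to change to reach 68.** Each route contradicts a printed input or adds a step that is not described:

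- two-sided alpha 0.01, normal approximation: 22/0.65 = 33.8, so 34 per group, 68 in total;
- 95% power, t-test, × 1.35 inflation: 25 × 1.35 = 33.75, so 34 per group, 68 in total;
- SD of about 2.31 with δ = 2, or δ of about 1.64 with SD 1.9: 22 evaluable per group at 80% power;
- alpha split over the three primary outcomes (0.05/3), t-test: 21/0.65 = 32.3, so 33 per group, 66 in total, which is close but not equal.

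The routes imply different designs, and the document does not allow a choice between them.

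**4. What 68 delivers if the printed inputs are right.**

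Evaluable per group: 34 × 0.65 = 22.1, so 22. For a two-sample t-test at two-sided 5%, the noncentrality is (δ/σ)√(n/2) = (2/1.9) × √11 = 3.49 on 42 degrees of freedom. Power is 92.7% (normal approximation 93.7%).

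On the same basis, power for 1.74 points is 84.3%, and the difference detectable with 80% power is 1.64 points. With no loss (34 per group), power for 2 points is 99%.

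**The case against.** The strongest reply has four parts.

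**The error is harmless in direction.** Under the stated inputs, 68 meets and exceeds 80% power even at the maximum loss foreseen. A reader who takes 80% at face value understates the trial's sensitivity, which is the cautious mistake. This stands and limits the severity.

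**It is a pilot in a condensed article.** A pilot need not be sized by power, and an article may omit steps such as an alpha split. That is fair, and an unreported step is as plausible as a misprinted figure. But the authors chose a power-based justification and printed its inputs and its result. The complaint is that these disagree, not that detail is missing.

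**The t-test is not the planned analysis.** This also stands. The effect is to come from a mixed model on weekly data, and its power depends on a within-person correlation that the article does not give. The article does not say, either, whether 1.9 is the SD of a score or of a change. Still, one difference and one SD support only a two-group comparison of means, so that is the fair way to check 68.

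**Sidedness is not stated.** True. Two-sided is an assumption, but a one-sided test moves the result further from 68.

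**Conclusion.** The target of 68 does not follow from the printed inputs. They give 50 by t-test or 48 by normal approximation at two-sided 5%, and 38 if one-sided. If all the inputs are right, 68 gives about 93% power for 2 points in a two-sample t-test after 35% loss, not 80%.

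Three stronger conclusions that a reader might draw are not supported:

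- *The trial is underpowered.* Under the stated inputs the pain comparison is larger than it needs to be. The margin would disappear only if an input differs from what is printed, such as an SD near 2.3.
- *The trial has 93% power.* That figure depends on SD 1.9 and a two-sided 5% t-test. It is not the power of the planned group-by-time test, which cannot be computed from this document.
- *The target should fall to 50, or a particular input is wrong.* Several different changes lead to 34 per group, and nothing in the text identifies the one used.

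Severity: should be fixed, not critical. The calculation itself is certain. The cause of the mismatch is unknown.

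**What to change.** Keep 68. First, go back to the original calculation, find the input or adjustment that produced 34 per group (for example a larger SD, a smaller difference, a smaller or split alpha, or a higher power), and state it together with the sidedness of the test.

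Only if there is no such input, restate the paragraph along these lines:

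> 68 patients randomised, about 22 evaluable per group after 35% loss, give about 93% power for a difference of 2.0 points, 84% for 1.74 points and 80% for 1.64 points. These are two-sample t-test figures, conditional on an SD of 1.9 and a two-sided 5% level; they are not the power of the mixed-model group-by-time test.

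The order matters, because printing these figures while the SD or the difference is misreported would replace one wrong statement with another. The cost is one check of the original calculation and one paragraph of wording. Recruitment and analysis stay as they are.

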### Statistical analysis

The effect of treatment will be separately analysed for each outcome using linear mixed models with time as a repeated factor, group as a fixed factor and participants as a random factor. The coefficient of the group x time interactions will provide estimates of the effects of interventions over time. Between-group differences in mobility-related goal attainment, at 6 months after randomisation, will be analysed with ordinal regression. To aid interpretation of goal attainment, the scores will also be dichotomised (goal met versus goal not met), and odds ratios calculated. Accelerometer data will be processed using ActiLife 6 software. Acceptable wear time will be set a priori and defined as 4 days or more of 10 h or more per day. All analyses will be performed by intention-to-treat and blinded to treatment group. Potential covariates that will be investigated are baseline pain and disability levels, number of previous treatments, symptom duration, co-morbidities, age and socioeconomic status.

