Another intervention that may be effective in improving adherence to exercise is health coaching. There is evidence that telephone-based health coaching interventions lead to positive changes in health behaviours. These include increased physical activity participation [14], improved nutrition [15], smoking cessation [16], and better management of chronic musculoskeletal conditions such as osteoarthritis [17]. Coaching interventions have a strong, evidence-based foundation in behaviour-change theories such as Social Influence Theory, Social Cognitive Theory, and the Transtheoretical Model [18] and can be effectively delivered by telephone [19]. There is evidence that health coaching via telephone has the potential to increase activity levels in patients with LBP when compared to usual physiotherapy care alone [20].

However, to the best of our knowledge, there are no studies of a post-treatment physical activity intervention consisting of mobile health and health coaching on long-term outcomes in patients with chronic LBP. Therefore, the primary aim of this RCT is to investigate the effec of a patient-centred physical activity intervention supported by health coaching and mHealth technology, including a mobile web app, tailored physical activity plan, goal setting, and feedback from affordable physical activity monitoring device (*FitBit*) in care-seeking, pain and disability in people with chronic LBP. Secondary outcomes will be physical activity participation and goal attainment. We hypothesise that the use of a patient-centred physical activity intervention will prevent clinical decline in patients who have received the benefits of conservative treatment for chronic LBP, empowering them to self-manage their LBP as well as to prevent worsening of LBP and reduce care seeking.

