### Group allocation

Random allocation to physical activity or standard care groups will occur after confirmation of eligibility and baseline assessment. Allocation will be blinded and performed using a computer-generated random allocation schedule operated by a remote researcher. The allocation of participants will be concealed by using sequentially numbered, sealed and opaque envelopes.

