*The IMPACT web app:* The IMPACT web app: A mobile web app will be built and hosted by the University of Sydney. The app will be customised specifically for the purposes of this project to allow participants to monitor their goals and their physical activities. Participants will be able to access the app at any time and write reports about their physical activity related goals to their health coach as well as receive coach-tailored feedback. In addition, each participant will receive a quick questionnaire every week to monitor their pain levels, based on the Numerical Rating Scale; disability, based on the Rolland-Morris disability questionnaire and care-seeking associated with LBP. This questionnaire was created specifically to this project. The health coach will have the ability to view the participant’s report and communicate with them by phone fortnightly to discuss their goals and update them according to their reports and feedback. Personalised messages constructed by the health coach will be sent every week to encourage participants to achieve their goals. In summary, the IMPACT web app will be designed to facilitate monitoring achievement and providing updates on participants’ goals, encouraging them to engage in physical activity and track potential adverse events.

*The standard care control group* will receive the ‘*Make your move – Sit less, be active for life!’* booklet and will be advised to work towards increasing their physical activity levels and achieving their two long-term goals as defined at baseline.

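### The goal-attainment analysis is limited to mobility-related goals, but the outcome is defined as two participant-chosen goals with no such limit

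*Protocol article*

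**What the plan says.** The Background names the outcome without qualification: "Secondary outcomes will be physical activity participation and goal attainment". The Secondary outcomes section measures it with the Goal Attainment Scale (GAS) and says "Two long-term goals will be defined by the participant at trial entry". It adds that in GAS "tasks are individually identified to suit the participant, and the levels are individually set around their current and expected levels of performance". The Interventions section, describing the control arm, refers to participants "achieving their two long-term goals as defined at baseline". Group allocation gives the order of events: "Random allocation to physical activity or standard care groups will occur after confirmation of eligibility and baseline assessment".

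The Statistical analysis section then states: "Between-group differences in mobility-related goal attainment, at 6 months after randomisation, will be analysed with ordinal regression". For interpretation, "the scores will also be dichotomised (goal met versus goal not met), and odds ratios calculated". The same section says that all analyses follow intention to treat and are run blind to group. It names a participant random factor for the linear mixed models, but says nothing either way about one for the ordinal regression.

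**The concern.** The outcome that is analysed is not the outcome that is defined. The qualifier *mobility-related* occurs only in the Statistical analysis section. The article does not say which goals qualify, who decides, or when. A goal about work, sleep or household tasks would be a legitimate GAS goal under the definition, yet would fall outside the analysis as worded. A participant with no qualifying goal would drop out altogether.

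Three things are at stake for one of only two secondary outcomes named in the Background:

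- **Precision.** The trial has 68 participants and already plans for up to 35% loss to follow-up.
- **The question.** The estimate would describe attainment of mobility goals among people who chose one, not attainment of participants' own goals.
- **Discretion.** With no stated rule, what counts as a mobility goal remains open when the data are analysed.

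A related point must be settled by any correction. Each person has two goals, and the article does not say whether the unit of analysis is the goal or the participant.

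**Working it through.** The protocol gives no figure for this analysis, so there is none to reproduce. The check has three parts.

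**1. Definition against analysis**

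| Section | Which goals | Content restriction |
|---|---|---|
| Background | Goal attainment | None stated |
| Secondary outcomes | Two long-term goals, set by the participant at trial entry | None stated |
| Interventions (control arm) | Two long-term goals, set at baseline | None stated |
| Statistical analysis | Mobility-related goal attainment at 6 months | Mobility only |

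The first three agree with each other and the fourth does not.

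**2. What a literal restriction would do**

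- *Timing.* Goals are set at baseline and allocation follows the baseline assessment, so goal content is a pre-randomisation characteristic.
- *Comparability.* A subset defined by that characteristic and labelled blind to arm is still a randomised comparison.
- *Precision.* Suppose a fraction f of participants has no qualifying goal. The number per arm falls from n to n(1 − f). With one score per participant, the standard error grows by about 1/√(1 − f). The article gives no basis for f, so no value is claimed here.

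**3. Conditional check: two goals entered as independent rows**

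Inputs:

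- Two goals per person (Secondary outcomes).
- 34 per arm (Sample size calculation), or about 22 per arm after 35% loss (34 × 0.65 = 22.1).
- Correlation ρ between a person's two goals. This is not in the document; 0.3 to 0.5 is assumed.

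Formulas:

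- Design effect = 1 + (2 − 1)ρ = 1 + ρ
- Ratio of the unadjusted to the correct standard error = 1/√(1 + ρ)
- Actual two-sided error at nominal 5% = 2[1 − Φ(1.96/√(1 + ρ))]

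| ρ | Design effect | SE ratio | 1.96/√(1 + ρ) | Actual error |
|---|---|---|---|---|
| 0.3 | 1.3 | 0.877 | 1.72 | 8.6% |
| 0.5 | 1.5 | 0.816 | 1.60 | 11.0% |

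This was checked by simulating five-level GAS scores under no treatment effect, with a rank test that corresponds to the proportional-odds score test (6,000 runs per setting). The correlation shown is on the latent scale; the correlations between the observed scores were 0.27 and 0.46.

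| Per arm | Latent correlation | Goals as independent rows | One summed score per participant |
|---|---|---|---|
| 34 | 0.3 | 7.9% | 4.7% |
| 34 | 0.5 | 10.3% | 5.0% |
| 22 | 0.3 | 7.7% | 4.6% |
| 22 | 0.5 | 10.4% | 5.1% |

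A separate simulation of the met/not-met odds ratio used 22 per arm and 20,000 runs. It gave 7.9% and 9.7% at correlations of about 0.33 and 0.49. Formula and simulations together put the error at about 8% to 11%, provided every participant contributes two goals as separate, unadjusted rows.

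**The case against.** The strongest reply is that the qualifier is a loose description and not a filter. The trial is about physical activity, and the control-arm text mentions working towards more activity and achieving the two goals in one sentence. Nothing states that other goals are excluded. This is a fair reading of intent, but it does not reconcile the sections. If no restriction is meant, the word should go; if one is meant, it contradicts the definition.

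Two stronger readings are tempting, and the document supports neither.

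- *A reader might infer that goals are selected after randomisation and that this breaks the intention-to-treat comparison.* The goals exist before allocation, and no later sorting step is described. Only the labelling of goals could come later, and that is inference. Blinded analysis would limit labelling by arm. What remains is a conflict with the intention-to-treat statement, through omitted participants, and not a demonstrated bias between arms.
- *A reader might infer that the two goals will be treated as independent.* The singular wording of the met/not-met split, and the absence of a participant term for the ordinal regression, make a goal-level analysis plausible. But the unit is not fixed. The GAS description, in which each participant has an individual outcome measure, fits one score per person equally well. The choice of a clustering term may properly be left to the full protocol or SAP, so its absence is not a fault here.

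The error figures also assume two goals from everyone. If a mobility filter were applied, some people would contribute only one goal, and the inflation would be smaller.

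**Conclusion.** The contradiction holds: three sections define the outcome by two unrestricted, participant-chosen baseline goals, and the analysis section restricts it to mobility-related ones. Taken literally, this costs precision and changes the question, by an amount the article does not allow one to calculate. It sits badly with the promise of intention to treat, but it does not show selection by arm.

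The 8% to 11% error rate is a conditional warning for whoever writes the correction. It rests on goal-level rows, no adjustment for pairing, two goals per person and an assumed correlation of 0.3 to 0.5. With one score per participant the error stays near 5%.

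The outcome is secondary in a pilot trial, so the primary conclusions do not depend on it. The correction is still worth making, because it is nearly free and makes the analysis match the stated outcome.

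**What to change.** Delete *mobility-related* from the Statistical analysis section and state that both baseline-defined goals of all randomised participants are analysed. Then state the unit in one of two ways:

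- one combined GAS score per participant, compared between arms, with a participant-level definition of goal met for the odds ratio; or
- each goal analysed individually, with an ordinal model for the score and a logistic model for met/not met, both with a participant random effect or cluster-robust standard errors.

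If a mobility restriction is really intended, carry it into the outcome definition and classify each goal at baseline, before allocation, by a written rule.

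The cost is about two sentences and a standard model option. No new data are needed if both goals are kept. If pairing is modelled, the confidence interval will be somewhat wider than one that ignores it.
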